### Study procedures and data collection

The three arms will complete a pre-activity demographic survey, the knowledge tests, and surveys of participation at other educational events. There is growing recognition of EBM in Italy and independent educational initiatives to improve general practice are becoming more common. During the trial, this additional education could be an important threat to internal validity. We will record these concurrent educational experiences in our sample and assess their effects in exploratory post hoc analyses.

Data will be collected from all participants using online instruments. The ECCE platform will manage and track all data collection, following up by e-mail the participants after 16 and 36 weeks. Although researchers are not blinded for the trial group allocation, they will not be able to interfere in collection.

The demographic survey will record sex, age, and years of practice; practice characteristics; preferred CME format; computer skills; ease in using the Internet; familiarity with EB information; frequency of attending residential and distant CME activities.

### Sample size and calculation of power

Based on a preliminary examination of test scores, we established that the smallest useful difference for this intervention was a 20% absolute improvement. Based on a preliminary test of 300 doctors, we found that a 28% absolute improvement was due to the intervention. We standardised the absolute improvement across different type of vignettes (five or ten questions). Therefore we calculated our sample size to detect a 0.7 standardized difference in the primary outcome, set the α error rate at 0.05 (two-sided), and the β error at 0.10 (90% power). This yielded a sample size of 45 practitioners per study arm. If the accrual period is six months, and the maximum follow-up period is six months with a loss during follow-up of 20% at the end of the study, the total number of practitioners to be randomised has been adjusted upwards to 162 (54 per intervention group).

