### Allocation to experimental arms

The Italian Cochrane Centre will produce the computer algorithm for the allocation sequence and will implement it on ECCE. Once doctors agree to participate, ECCE will assign doctors to one of the three arms using a balanced randomisation scheme. Researchers will be unable to manipulate the randomisation sequence or interfere with the ECCE registration process. In Figure 6, we present a flow chart outlining the progress of participants through the study. This protocol follows the recommendations of the Consort Statement [Additional file 1] [24].

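### The protocol requires 45 doctors per arm and assumes 20% loss, but 54 randomised per arm leave about 43; power stays at about 90%

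*Protocol article*

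**What the plan says.** All the figures are in the protocol article, Sample size and calculation of power. The target is given as "we calculated our sample size to detect a 0.7 standardized difference in the primary outcome". The error rates are "set the α error rate at 0.05 (two-sided") and "the β error at 0.10 (90% power"). The result is reported as "This yielded a sample size of 45 practitioners per study arm". The section then allows for "a loss during follow-up of 20% at the end of the study" and concludes that "the total number of practitioners to be randomised has been adjusted upwards to 162 (54 per intervention group").

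The factor of three is confirmed under Allocation to experimental arms: "ECCE will assign doctors to one of the three arms using a balanced randomisation scheme". The article does not say how the loss was turned into extra recruitment, or which formula produced 45.

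**The concern.** An allowance for loss is meant to ensure that the required number is still there after the loss has happened. That calls for dividing the required number by the fraction retained. Multiplying it by one plus the loss fraction gives too small a number, because the loss applies to everyone randomised and not only to the required number. The stated 54 is exactly what multiplication gives.

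What is at stake is the consistency of a headline design figure. Anyone who later checks the trial against its target of 45 per arm would find a shortfall even if loss were exactly as planned. The loss is stated for the end of the study, so the shortfall falls on the last knowledge test, at about 36 weeks.

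**Working it through.** **Inputs**, all from Sample size and calculation of power unless noted: standardised difference d = 0.7; two-sided α = 0.05; power 90%; required number 45 per arm; loss 20%; randomised 54 per arm, 162 in total; three balanced arms (Allocation to experimental arms).

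**1. Reproducing the base number.** Normal approximation for two means, per arm:

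n = 2(z₀.₉₇₅ + z₀.₉₀)² / d² = 2(1.960 + 1.282)² / 0.49 = 42.9, so 43.

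The two-sample t-test gives 43.87, so 44. The stated 45 is one or two above what the inputs need, which is a harmless margin.

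**2. Reproducing the adjusted number.** 45 × 1.2 = 54, and 54 × 3 = 162. Both match the protocol exactly.

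**3. What 54 per arm leaves.** 54 × (1 − 0.20) = 43.2 per arm. Over three arms this is 129.6, against 3 × 45 = 135.

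**4. What 45 per arm would take.** 45 / (1 − 0.20) = 56.25, so 57 per arm and 57 × 3 = 171 in total. That is 9 more than 162 (9 / 162 = 5.6%). As a check, 57 × 0.8 = 45.6.

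**5. Break-even loss.** 1 − 45/54 = 16.7%. Above this, fewer than 45 per arm remain.

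**6. Effect on power.** Two arms of equal size, d = 0.7, two-sided 0.05. The normal approximation is Φ(d√(n/2) − 1.960); the t-test column uses the noncentral t distribution.

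| Evaluable per arm | Normal approximation | t-test |
|---|---|---|
| 45 | 91.3% | 90.7% |
| 44 | 90.7% | 90.1% |
| 43 | 90.1% | 89.4% |

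For 43 by the normal approximation: 0.7 × √21.5 = 3.246; 3.246 − 1.960 = 1.286; Φ(1.286) = 90.1%. Going from 45 to 43 costs 1.2 to 1.3 percentage points.

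**The case against.** A reader might infer that the trial misses its 90% power. The figures do not support that as a general statement. The article does not name the formula behind 45. By the normal approximation 43 per arm are enough, and 43.2 remain; by the t-test 44 are needed, and 43 give 89.4%. Whether 90% is met turns on the approximation, and the gap is under one percentage point. The margin already in 45 absorbs nearly all of the shortfall. This part of the objection stands.

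A reader might also take it as established that the loss was added by multiplying by 1.2. That is an inference. Starting from the normal-approximation figure, 43 / 0.8 = 53.75 also rounds up to 54. But the article reports 45, not 43, as the result of its calculation. If 43 was the real base, the printed 45 is the figure to correct. The mismatch remains either way; only its cause is uncertain.

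Three further points limit the power figures without removing the mismatch:

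- Statistical analyses plans a repeated-measures ANOVA over three tests. A two-group comparison at one time is only a yardstick for it, and the article does not give the correlation between tests that a closer calculation would need.
- The abstract describes the classical comparison as groups one and two together against group three. Pooled in that way, 86 against 43 gives about 96% power: 0.7 × √(86 × 43 / 129) = 3.748, and Φ(3.748 − 1.960) = 96%. Table 1 instead sets each ECCE arm separately against arm III, where the 43-per-arm figures apply.
- The 20% is a planning assumption. The distance from 20% to the break-even of 16.7% is 3.3 points, which is within ordinary planning uncertainty.

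**Conclusion.** The concern holds as an internal inconsistency of small consequence. With 20% loss, the stated 162 doctors leave about 43 per arm, not the stated 45. Nothing elsewhere in the article repairs this. The count is missed by about 2 per arm. Power for a two-arm comparison is 89.4% to 90.1%, so about 90%, against 90.7% to 91.3% with 45.

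The count rests only on the printed figures. The power range also assumes a two-sample comparison of two arms at 0.7 standard deviations and two-sided 0.05. The mismatch brings no bias and changes neither the design nor the analysis.

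**What to change.** Replace the last step of the sample size section with a sentence that states what the planned number delivers, and name the test so that the power is not read as that of the repeated-measures analysis:

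> 162 doctors randomised (54 per arm) leave about 43 per arm after 20% loss, giving about 89–90% power for a 0.7 SD difference between two arms (two-sample comparison); 45 per arm are retained if loss does not exceed 16.7%.

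The cost is one sentence and a slightly less favourable power figure. No extra enrolment is needed. If the authors prefer to keep 45 evaluable per arm as a firm requirement at 20% loss, the matching number to state is 171 (57 per arm), which is 9 more doctors.

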### Statistical analyses

Knowledge test data will be analysed using repeated-measure analyses of variance (ANOVA), reporting the partial omega squared (ù2) effect size with corresponding 95% confidence interval. Scores for the    knowledge test scale will be subjected totwo-by-three [TO TWO-BY-THREE] repeated-measures ANOVA having: 1) one between-subjects factor (ECCE lot A and ECCE lot B) and one within-subject factor (pre-test, post-test one and post-test two) for the incomplete block design trial; 2) one between-subjects factor (ECCE set and control) and one within-subject factor (pre-test, post-test one and post-test two) for the classical trial. Tests of Sidak-adjusted simple main effects will be used for post-hoc mean comparisons as needed. Orthogonal planned contrasts will be formulated for the knowledge test data to verify knowledge retention. We do not expect the data sets to follow normal distributions and assumptions completely. If this is the case, we will do nonparametric and robust analyses to explore differences in medians or distributional shapes. If nonparametric analysis yields similar interpretations and conclusions, we will focus on the parametric results.

Additional analyses will include examination of the relationship between knowledge test outcomes and potential moderator variables including sex, age, and years of practice, speciality (*e.g*., general internal medicine versus general surgery); preferred CME format; computer skills; ease using the internet; familiarity with and readiness to use EB information; study drop-out; satisfaction with learning experience, and frequency of attending residential and distant CME activities. For these analyses, we will use parametric methods (regression, repeated-measures ANOVA, analyses of covariance (ANCOVA)) and nonparametric methods (Wilcoxon-Mann-Whitney test, χ^2 ^test of independence and γ measure of association) as needed, based on the data. Holm's modified Bonferroni corrections will be applied to check experimental error (*e.g*., in exploratory analyses). Analyses will be done based on an intention-to-treat basis, whether or not doctors logged and took credits. We will restrict the explanatory analysis to those doctors who took credits. All the analyses will consider *p *= 0.05 as significant (two-sided).

SAS version 9.0 statistical software (SAS Institute, Inc, Cary NC) will be used.

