### Outcomes measures and measurements

The primary outcome will be basic knowledge of the *Clinical Evidence *contents assessed through the scores from the clinical vignettes. The test will consist of fixed and multiple-choice questions from the selected valid, reliable vignettes and will be administered before (pre-test), immediately after (approximately 16 weeks after enrolment, post-test one), and six months after the intervention (approximately 36 weeks after enrolment, post-test two) (see Figure 6).

To reduce the risk of a test-training effect (practice effects or memory of the first administration will influence post-test performance) at each test section ('pre-test', 'post-test one' and 'post-test two'), we will randomly select two vignettes from lot A and two from lot B to avoid repetition. Therefor, each participant will have only a limited probability (approximately zero) of test/re-testing the same vignette from one assessment to another. The questionnaire will investigate the same *Clinical Evidence *knowledge for intervention and control chapters. This random sampling of outcomes with high psychometric standards will eliminate any interactions between the causal relationship and the classes of outcomes studied or not studied within the same group of vignettes [25]. To prevent participants from guessing which vignettes will be evaluated, we will add a number of "distracter" vignettes to lots A and B. All groups will also rate their satisfaction with the information source and its perceived value for their medical education and clinical practice.

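### The planned repeated-measures ANOVA uses the pre-test as an outcome level; using it as a covariate would be at least as precise as the change contrast, at no cost in data

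*Protocol article*

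**What the plan says.** The Statistical analyses section fixes the model for the knowledge test: "Knowledge test data will be analysed using repeated-measure analyses of variance (ANOVA"). It is a two-by-three layout with one between-subjects factor and one within-subject factor, whose levels are pre-test, post-test one and post-test two. Orthogonal contrasts for retention and Sidak-adjusted simple effects follow. ANCOVA is named only for the additional moderator analyses. The same section adds: "Analyses will be done based on an intention-to-treat basis, whether or not doctors logged and took credits".

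The Sample size section aims to "detect a 0.7 standardized difference in the primary outcome", with "set the α error rate at 0.05 (two-sided") and "the β error at 0.10 (90% power"). This gives 45 per arm, raised to 54 for "a loss during follow-up of 20% at the end of the study". The sentence before the 0.7 reads "We standardised the absolute improvement across different type of vignettes (five or ten questions"). No pre-post correlation is given.

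On test content, the Outcomes section says that at each session "we will randomly select two vignettes from lot A and two from lot B to avoid repetition".

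**The concern.** When the pre-test is an outcome level, the evidence for treatment lies in the group-by-time interaction or in a contrast of change from pre-test to post-test. That contrast carries the noise of both tests in full. If the two tests correlate weakly, subtracting the pre-test adds more noise than it removes. A weak correlation is plausible here because each session uses only two vignettes per lot and avoids repeating them.

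The sample size appears to rest on a plain comparison of two means. If so, the planned analysis may not have the power that the calculation promises, although the same data would support a more precise estimate.

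The second issue is missing tests. A classical repeated-measures ANOVA needs all three scores from each doctor. With 20% loss expected, that would be an analysis of completers.

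**Working it through.** **1. The plan's own figure.** Two means, difference 0.7 SD, two-sided α = 0.05, 90% power:

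n = 2(1.96 + 1.2816)² / 0.7² = 42.9, so 43 per arm; 44 with the t distribution. The stated 45 is within 2 of this, so it reproduces as a two-group comparison that uses no pre-post correlation. Power at 45 per arm is 90.7% (t).

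**2. Completers.** 54 × 0.8 = 43.2, so 43 per arm. The plain two-group comparison at 43 per arm has 89.4% power (t).

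**3. Precision of the two analyses.** Take the single-test SD as 1 at each test and r as the pre-post correlation.

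- Change contrast: variance per doctor 2(1 − r).
- Post-test adjusted for pre-test: residual variance 1 − r².
- Ratio, adjusted to change: (1 − r²) / [2(1 − r)] = (1 + r)/2, which never exceeds 1.

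Adjustment is therefore at least as precise at every r, apart from the one degree of freedom spent on the slope. The change contrast is also less precise than ignoring the pre-test when 2(1 − r) > 1, that is when r < 0.5.

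**4. Power if 0.7 is in single-test SD units.** Noncentral t, one lot, effective difference 0.7/√[2(1 − r)] for change and 0.7/√(1 − r²) for adjusted. The values of r are assumed.

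| r | Change, 43 v 43 | Adjusted, 43 v 43 | Change, 86 v 43 |
|---|---|---|---|
| 0.2 | 72% | 91% | 84% |
| 0.3 | 77% | 92% | 88% |
| 0.4 | 83% | 94% | 92% |
| 0.5 | 89% | 96% | 96% |

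Example at r = 0.3: 0.7/√1.4 = 0.592 gives 77%; 0.7/√0.91 = 0.734 gives 92%. The 86 v 43 column pools arms one and two against arm three, as the Abstract describes the classical comparison.

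The two-degree-of-freedom group-by-time test behaves similarly. At 45 per arm with a sustained effect and equal correlations it has 77, 83, 88 and 94% at the same r values. If half the effect has faded by post-test two, it has 64, 70, 77 and 85%.

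**5. Power if 0.7 is in change-score SD units.** The change contrast at 43 v 43 has 89% whatever r is, so there is no shortfall. The adjusted analysis has effective difference 0.7·√[2(1 − r)]/√(1 − r²) = 0.7·√[2/(1 + r)]. At r = 0.7 this is 0.759, giving 94%; at smaller r it is higher.

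**6. Missing tests.** A classical fit would analyse about 43 of 54 doctors per arm if the 20% loss falls only at the end. If 20% independently missed each post-test, complete cases would be 54 × 0.8² = 34.6 per arm.

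**The case against.** A group-by-time ANOVA is a valid test under randomisation, so the choice is one of efficiency. The shortfall below 90% is conditional on three things the article does not settle:

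- **Which SD.** The sample-size text speaks of standardising the improvement. If 0.7 is in change-score SD units, the shortfall disappears. The other reading is supported by the wording that ties 0.7 to the primary outcome, which is defined by vignette scores. The text does not decide between them.
- **Which r.** A modest value is a reasonable guess from the vignette sampling, but no value is given.
- **Which comparison.** The 43 v 43 single-lot figures are near the worst case. Pooling helps, as shown above. In the block design each doctor also supplies intervention and control data. If the two lots were combined as a within-doctor difference of changes, with zero correlation between lots (an assumption), the effective difference at r = 0.2 would be 1.4/√(4 × 0.8) = 0.783, giving about 95%.

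These points stand, and they limit the claim. A reader might infer that the trial is underpowered as designed; the documents do not support that without those assumptions.

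A reader might also infer that the ANOVA contradicts the intention-to-treat statement by dropping doctors who miss a test. The text does not say so. Its intention-to-treat sentence concerns platform use, not missed tests; no exclusion is written; and the fitting procedure is not named. A repeated-measures model can be fitted by likelihood to all available scores. Handling of missing tests may also be set out in a fuller document not shown, so its absence is not held against the article.

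Finally, covariate adjustment does not beat every alternative. With a sustained effect and r = 0, the group effect averaged over all three tests has 97% power at 45 per arm against 91% adjusted, because it pools both post-tests. It does not estimate the six-month difference, however, and nothing in the article says it would be read as the result.

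**Conclusion.** The point holds as an available improvement, not as an error. The article commits to treating the pre-test as an outcome level and keeps ANCOVA for secondary analyses. Adjusting for the pre-test is at least as precise as the change contrast at every r and under either reading of the 0.7.

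The gain is largest, 91% against 72% at r = 0.2, for a single-lot 43 v 43 comparison with 0.7 in single-test SD units. On that reading the change contrast misses the planned 90% when r is below about 0.5. With 86 v 43 it misses only at the lower correlations, roughly 0.3 and below. With 0.7 in change-score units it does not fall short of plan at all.

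On missing tests, only a conditional statement is justified: if the ANOVA is fitted classically, it analyses completers, which is hard to reconcile with intention to treat when 20% loss is expected.

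**What to change.** Make the primary analysis a likelihood-based (REML) linear mixed model for post-tests one and two, with the same-lot pre-test score as covariate, including every randomised doctor with at least one post-test. Take the treatment contrast at post-test two as the primary estimate, in line with the Abstract, which places the primary outcome at least six months after the intervention. Keep the planned ANOVA as a sensitivity analysis. State whether the 0.7 is in single-test or change-score SD units.

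The cost is a change of analysis wording and a slightly more complex model. No extra data or doctors are needed, since the pre-test is already collected. Doctors with no post-test contribute nothing to this model, so they still need a sensitivity analysis.

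### The only effect size promised with a confidence interval, partial omega squared, cannot be read against the protocol's own 20% usefulness threshold

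*Protocol article*

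**What the plan says.** Under Sample size and calculation of power, the protocol article sets its yardstick on the score scale: "the smallest useful difference for this intervention was a 20% absolute improvement". It adds that in a preliminary test of 300 doctors "we found that a 28% absolute improvement was due to the intervention". It then changes scale: "we calculated our sample size to detect a 0.7 standardized difference in the primary outcome". No SD is given.

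Under Statistical analyses it states: "Knowledge test data will be analysed using repeated-measure analyses of variance (ANOVA), reporting the partial omega squared", and attaches a 95% confidence interval to that measure. The ANOVAs have two groups and three test occasions. The same paragraph also provides for:

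- Sidak-adjusted simple main effects for comparing means, where needed;
- orthogonal planned contrasts on retention;
- nonparametric and robust analyses, including differences in medians, if distributional assumptions fail.

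None of these three is given an estimate or an interval to report. Table 1, under Study design, words the hypotheses by direction: scores should rise on the trained lot and stay unchanged in the control comparison.

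**The concern.** The protocol defines a worthwhile result in percentage points and commits to an interval on a different scale. Nothing in the text connects the two. An interval for partial omega squared bounds a proportion of variance; it does not tell a reader whether a gain of 20 points has been reached, excluded or left open.

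The Aim of the study section asks separate questions about acquiring knowledge, retaining it beyond six months, and superiority to print. One figure for a group-by-time effect with two degrees of freedom does not answer them separately. The Background says the agency sponsored ECCE partly to be sure that distributing the compendium justified its cost, so the size of the gain matters as well as its significance.

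**Working it through.** **Inputs.** From Sample size and calculation of power: 20% and 28% absolute improvement, standardised difference 0.7, two-sided alpha 0.05, power 90%, 45 per arm. From Statistical analyses: two groups and three occasions, so the group-by-time effect has 2 degrees of freedom. All SDs below are assumptions. Two of them follow from the protocol's own figures: 20/0.7 = 28.6 if 0.7 stands for 20 points, and 28/0.7 = 40 if it stands for 28. The text does not say which.

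**Step 1: reproduce the plan's figure.** n per arm = 2(z₀.₉₇₅ + z₀.₉₀)²/d² = 2(1.960 + 1.282)²/0.49 = 42.9, so 43. The noncentral t gives 44 (power 0.901), and 45 per arm has power 0.907. The plan states "This yielded a sample size of 45 practitioners per study arm"; this reproduces to within two doctors.

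**Step 2: sign and SD in a simple two-group comparison (illustration only).** With two equal groups, population omega squared = d²/(d² + 4). Only d² enters, so d = +0.7 and d = −0.7 both give 0.49/4.49 = 0.109. The sample version with 45 per arm uses F = 45d²/2 and (F − 1)/(F − 1 + 90). For d = 0.7, F = 11.03 and 10.03/100.03 = 0.100.

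| Assumed SD | d for 20 points | Population value for 20 points | Sample value, 45 per arm | Points matching a population value of 0.109 (0.7 × SD) |
|---|---|---|---|---|
| 20 | 1.0 | 0.200 | 0.193 | ±14 |
| 28.6 | 0.7 | 0.109 | 0.100 | ±20 |
| 40 | 0.5 | 0.059 | 0.049 | ±28 |

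One true 20-point difference spans roughly a fourfold range in the sample value (0.193/0.049 = 3.9). Conversely, one value of omega squared can lie below, at or above 20 points.

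**Step 3: the 2-df group-by-time effect.** Take the arm differences at the three tests, centre them on their mean, halve them, and average the squares to get s. The population value is s/(s + residual variance). For (0, 20, 20) the mean is 13.33, the halved deviations are −6.67, 3.33 and 3.33, and s = (44.4 + 11.1 + 11.1)/3 = 22.2. With an assumed residual SD of 20, 22.2/422.2 = 0.053.

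| Arm difference at pre-test, post-test one, post-test two | Meaning | Value |
|---|---|---|
| 0, +20, +20 | gain, retained | 0.053 |
| 0, −20, −20 | lasting loss | 0.053 |
| 0, +20, 0 | gain, then lost | 0.053 |
| 0, 0, +20 | late gain | 0.053 |

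The four patterns coincide because s is the same in each. The residual SD here is not the score SD of Step 2, so 0.053 and 0.193 should not be compared.

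**The case against.** The strongest reply is that naming one effect size does not exclude others. The text never says that partial omega squared is all that will be reported. Mean comparisons and retention contrasts are planned and are signed, Table 1 interprets results by direction, and a condensed article may leave lists of means and differences to a fuller document. This stands to a large degree. A reader might infer that the trial will be unable to tell benefit from harm; the document does not support that.

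A reader might also infer that a trivial gain and a useful one would look identical. That is too strong. At a fixed SD omega squared rises with the effect, and the SD will be known after the trial. For a one-degree-of-freedom contrast it can then be converted to an absolute size, though still without a sign. For the 2-df effect it cannot.

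It can further be said that the 20% figure appears only in the sample-size section and is not a decision rule, and that a standardised scale suits vignettes of five or ten questions. Both are fair. But the protocol calls 20% the smallest difference that is useful, which concerns interpretation, and a percentage score also accommodates different numbers of questions.

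What the reply does not remove is that the article makes a positive choice of the measure that carries the interval, and that measure is not on the scale of its own threshold. A test, or arm means without an interval for their difference, does not fill the gap.

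**Conclusion.** The point holds in limited form. Partial omega squared is the only effect size with a confidence interval that the protocol commits to for the main knowledge analysis, and that interval cannot be read against the 20% absolute improvement. Direction would be visible from the planned comparisons of means; what is missing is an interval for the difference in points.

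The hypothesis tests and the sample size are not in question. The values 0.19, 0.10 and 0.05 illustrate dependence on the SD in a plain two-group comparison and must not be taken as values of the planned 2x3 statistic. The equality of the four patterns within the 2-df effect does not depend on the assumed residual SD; only the value 0.053 does. The conclusion takes a 20% absolute improvement to mean 20 points on a percentage score, the natural reading. This is a worthwhile correction to the main estimate, not a threat to the trial's validity.

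**What to change.** In Statistical analyses, name as the main estimate the between-arm difference in percentage-score points, with a 95% confidence interval, at post-test one and at post-test two, allowing for the pre-test score:

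- **Block design:** trained minus untrained arm within each lot's scores, that is, arm I minus arm II on lot A and arm II minus arm I on lot B. Combine the two by adding tested lot to the model.
- **Classical design:** ECCE minus print.

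State that these intervals will be interpreted against 20 points, and keep partial omega squared as a supplement.

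The cost is small but is more than wording. The block-design ANOVA as described has only arm and time, with no factor for the lot being tested, so the trained-minus-untrained estimate needs lot-specific scores or an added lot factor. Each test already draws two vignettes from each lot, so no new data and no change in sample size are needed.
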